### Diagnostic criteria

2.9

The diagnosis of plaque psoriasis is prepared with reference to the “Chinese Psoriasis Diagnosis and Treatment Guidelines (2023 Edition)” (38). Diagnosis is based on characteristic features including well-demarcated, dark-red plaques with silvery-white scaling, classic signs (e.g., candle-grease sign, Auspitz’s sign), and a chronic, relapsing course.

### Diagnostic criteria for blood stasis pattern in psoriasis

2.10

According to the “2017 Consensus on the Treatment of Psoriasis with Traditional Chinese Medicineissued” by the Chinese Society of Dermatology (39), the diagnosis of Blood Stasis Syndrome can be established when two primary symptoms (chronic, recurrent lesions with dark-red or violaceous coloration) and at least two secondary symptoms (dark-colored menstrual blood or clots in female or experience localized pain) are present, supported by tongue and pulse signs (purple or dark tongue body with ecchymosis or petechiae).

### Sample size calculations

2.11

Based on our pilot data, the verum ACE achieved an improvement rate of 60%. Since no sham-controlled acupuncture trials for psoriasis are available, we derived the sham group response rate from the placebo effect observed in psoriasis pharmacological trials, which was approximately 25% as reported in the literature (40). Sample size estimation was performed using the standard formula for comparing two independent proportions (two-sided test, *α* = 0.05, power = 80%):

$$n1=n2=\frac{{\left(Z_{1-\alpha /2}+Z_{1-\beta }\right)}^{2}\times [p_{1}(1-p_{1})+p_{2}(1-p_{2})]}{{\left(p_{1}-p_{2}\right)}^{2}}$$

Where p_1_ = 0.60, p_2_ = 0.25, Z_1 − α/2_ = 1.96, and Z_1 − β_ = 0.84. The calculated sample size was 28 participants per group. After adjusting for a 20% dropout rate, the final sample size was determined to be 35 participants per group (total 70 participants).

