#### Primary efficacy endpoints

2.19.1

We selected the PASI and BMI as primary endpoints, as they are well-established metrics for psoriasis lesions and obesity, respectively. Through expert panel discussion, a consensus-based decision was made to define the primary outcomes as the absolute change in PASI improvement score and the absolute change BMI at Week 8. The formulas for calculation are presented below:

(1) PASI improvement rate at week 8 = (baseline PASI score - PASI score at Week 8) / baseline PASI score × 100%.(2) Change in BMI at week 8 = baseline BMI - BMI at Week 8.

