All statistical analyses will be performed using a pre-specified statistical analysis plan. The primary analysis will use a linear mixed-effects model for repeated measures to analyze the changes from baseline in the continuous PASI score and BMI at week 8. As these will be pre-specified co-primary endpoints evaluating distinct therapeutic dimensions, no adjustment for multiple will be applied. Each endpoint will be tested independently at a two-sided significance level of *α* = 0.05. A similar approach will be used for continuous secondary outcomes (e.g., DLQI, WC, lipid profiles, inflammatory markers) will be presented as mean ± standard deviation for continuous variables and as frequencies (n) and percentages (%) for categorical variables. Within-group comparisons (e.g., baseline vs. Week 8) will be analyzed using paired t-tests for normally distributed data or Wilcoxon signed-rank tests for non-normally distributed data. Between-group comparisons will be performed using independent samples t-tests or Mann–Whitney U tests. Categorical outcomes will be compared using Chi-square tests (or Fisher’s exact tests). A two-sided *p*-value < 0.05 will be considered statistically significant. All analyses will follow the intention-to-treat principle. For exploratory outcomes assessed at extended time points (Weeks 12, 16, 24, and 32), the analysis will be primarily descriptive. Data are presented as mean ± standard deviation (or median with interquartile range for non-normally distributed data). No formal between-group hypothesis testing will be performed for these time points, as the data will be intended to illustrate long-term trends rather than confirm treatment efficacy. All statistical tests will be two-sided with a significance level of *α* = 0.05.

Pre-specified subgroup analyses will be performed to explore the heterogeneity of treatment effects on the primary outcomes. Interactions between treatment group and the following baseline covariates will be tested using the linear mixed model by including an interaction term: sex (male, female), age (< 45 years, ≥ 45 years), baseline BMI (< 28 kg/m^2^, ≥ 28 kg/m^2^), baseline disease duration (< 5 years, ≥ 5 years)

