## Limitation

4

Although the PASI-based sample size calculation is more directly aligned with the primary endpoint of psoriasis, the absence of robust sham-controlled RCT data means that estimates derived solely from PASI assumptions, rather than BMI-based parameters, may still carry inherent uncertainty. Despite the use of a rigorous blinding design (such as sham embedding needles and independently prepared tool kits by a third party), potential bias from the operating physicians may still influence the results. In addition, although the sham embedding group simulated the needle insertion and pushing actions, there is an inherent difference from real embedding in terms of the physical stimulation of “thread implantation,” which may affect the equivalence of the placebo effect. We acknowledge the potential confounding effects of concomitant medications. Although we required patients to maintain stable regimens for underlying comorbidities throughout the trial, the complex interplay of medications commonly used in this population may still influence weight and inflammatory outcomes. As an exploratory trial, this study did not implement a drug washout period or perform subgroup analyses based on specific medication classes. Future studies should incorporate longer baseline observation periods or include medication usage as covariates to better delineate the treatment effect of acupoint catgut embedding. In addition, the primary endpoint of this study was set at week 8, with extended follow-up for secondary endpoints up to week 32. However, the sustainability of long-term efficacy after short-term intervention still requires further research, especially considering the chronic nature of psoriasis and the risk of weight rebound.

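### The stated 80% power is for a two-proportion comparison that is not a planned primary test, and BMI, the second primary endpoint, has no power basis

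*Protocol article*

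**What the plan says.** Section 2.11 (Sample size calculations) states that "Sample size estimation was performed using the standard formula for comparing two independent proportions", with "two-sided test, *α* = 0.05, power = 80" per cent. The verum input is a pilot result: "the verum ACE achieved an improvement rate of 60" per cent. For the control input, "we derived the sham group response rate from the placebo effect observed in psoriasis pharmacological trials", "which was approximately 25% as reported in the literature". The result is 28 per group, raised to 35 per group (70 in total) for 20% dropout.

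Section 2.19.1 (Primary efficacy endpoints) names two primary outcomes at week 8, one for PASI and one for BMI. It describes both as absolute changes but gives a percentage formula for PASI: "PASI improvement rate at week 8 = (baseline PASI score - PASI score at Week 8) / baseline PASI score × 100" per cent. The BMI outcome is a simple difference from baseline.

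Section 2.21 (Statistical methods) uses a linear mixed-effects model "to analyze the changes from baseline in the continuous PASI score and BMI at week 8", each endpoint tested at two-sided 0.05 without adjustment. Chi-square and Fisher tests are mentioned only in general terms, for categorical outcomes.

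Section 4 (Limitation) comments: "Although the PASI-based sample size calculation is more directly aligned with the primary endpoint of psoriasis". The same sentence concedes that the estimates rest on PASI assumptions alone and not on BMI parameters.

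**The concern.** A power statement is useful only if it refers to the test that decides the trial. Here the powered comparison is of two proportions, while both primary tests compare continuous changes. No PASI cut-off that would make a patient a responder appears anywhere in the article.

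The inputs are also ambiguous. Section 2.11 calls the verum figure an improvement rate and the sham figure a response rate, while section 2.19.1 defines the PASI improvement rate as each patient's own percentage change. If 60% and 25% are mean percentage changes, the binomial variance p(1 − p) does not describe their spread. If they are shares of responders, no primary analysis compares those shares.

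BMI has the same standing as PASI among the primary endpoints, yet the article gives no target difference, SD or power for it. A reader who takes 80% as the power of the primary results would be misled about both endpoints, and a non-significant BMI result could not be set against any stated power.

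**Working it through.** **1. Reproducing the plan's figure.** Inputs from section 2.11: p1 = 0.60, p2 = 0.25, z = 1.96 and 0.84, dropout 20%.

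n = (1.96 + 0.84)² × [0.60 × 0.40 + 0.25 × 0.75] / (0.60 − 0.25)² = 7.84 × 0.4275 / 0.1225 = 27.36, rounded up to 28. Then 28 / 0.80 = 35 per group, 70 in total. This agrees with the article. With 28 per group the same unpooled formula gives 80.9% power. The arithmetic is sound for a binary endpoint.

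**2. Matching it to the primary tests.**

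| Element | Section 2.11 | Sections 2.19.1 and 2.21 |
|---|---|---|
| Endpoint | proportion improved or responding, no threshold given | continuous week-8 change in PASI; continuous week-8 change in BMI |
| Test | two independent proportions | linear mixed-effects model |
| BMI inputs | none | BMI is a primary endpoint |

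**3. What 28 or 35 per arm gives for a continuous endpoint.** For a simple two-mean comparison at two-sided 0.05, the standardised difference d with 80% power is approximately (1.96 + 0.84) × √(2/n): 0.75 for n = 28 and 0.67 for n = 35. The noncentral t distribution gives 0.76 and 0.68.

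**4. Reading A: 60% and 25% are mean percentage improvements.** The formula then implicitly uses a common SD of √(0.4275 / 2) = 0.462, about 46 percentage points. The article gives no SD, so those below are assumptions. With a 35-point difference and 28 per arm (noncentral t):

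| Assumed SD (points) | d = 35/SD | Power |
|---|---|---|
| 30 | 1.17 | 99% |
| 40 | 0.88 | 90% |
| 60 | 0.58 | 57% |
| 70 | 0.50 | 45% |

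The range lies on both sides of 80%.

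**5. Reading B: they are responder shares.** Assume a normal underlying variable with common SD, cut at one threshold. Then d = z(0.60) − z(0.25) = 0.253 + 0.674 = 0.93, and a continuous test with 28 per arm has about 93% power.

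**6. BMI.** Neither reading supplies anything for BMI. As an illustration with assumed SDs of 8-week BMI change of 0.8 to 1.5 kg/m², 80% power at 28 per arm requires a difference of 0.76 × 0.8 = 0.61 to 0.76 × 1.5 = 1.14 kg/m². At 35 per arm it requires 0.68 × 0.8 = 0.54 to 0.68 × 1.5 = 1.02 kg/m².

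**The case against.** The strongest reply is that the mismatch may be harmless or even conservative for PASI. Dichotomising discards information, so if the inputs are responder shares, the continuous test could have more than 80% power. Adjustment for baseline in the mixed model might add some. This stands as far as it goes: the direction of the error for PASI is unknown. It depends, however, on a threshold that the article does not define, and it does not reach BMI.

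A second reply is that section 4 already discloses the BMI gap and calls the study exploratory. The disclosure is fair and should be credited, but it confirms that BMI has no power basis and does not supply one. The same sentence still presents the calculation as aligned with the psoriasis endpoint, although it does not match that endpoint's analysis.

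Three stronger readings are tempting and are not supported:

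- A reader might infer that the trial is underpowered. Without SDs, the documents cannot show that.
- A reader might quote 0.80 × 0.80 = 64% as the power to succeed on both endpoints. That presumes 80% for each and a rule that both must succeed. Section 2.21 states no such rule and tests each endpoint on its own.
- A reader might count the drug-placebo source of the 25% as part of this error. The article states the source and its reason, namely that no sham-controlled acupuncture trials in psoriasis were available. Whether another rate is more plausible is a separate judgement.

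**Conclusion.** The point holds. The 80% in section 2.11 is correctly computed for 60% against 25% as proportions, but it is the power of a test that is not among the primary analyses, and BMI has no power basis at all.

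The size of the discrepancy cannot be fixed from the documents. For PASI, power at 28 per arm is about 99% to 45% over assumed SDs of 30 to 70 points if the inputs are mean percentage changes, and about 93% if they are responder shares of a normal variable with common SD. For BMI it is undetermined. What can be stated without trial-specific assumptions about effect or spread is the detectable standardised difference for a simple two-mean comparison: about 0.76 with 28 evaluable per arm and about 0.68 with 35.

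**What to change.** Keep N = 70 and revise section 2.11 as follows.

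1. Say whether 60% and 25% are responder shares (with the threshold) or mean percentage changes.
2. Delete the two-proportion calculation, or label it as not relating to the primary analysis.
3. State instead, for example: *For a simple two-mean comparison at two-sided 0.05, the trial has 80% power for a standardised difference of about 0.76 with 28 evaluable participants per arm (about 0.68 with 35), for PASI change and for BMI change separately.*
4. Translate this into PASI and BMI units with pilot SDs where they are held, and otherwise over an assumed range that includes favourable and unfavourable values. The article reports only one pilot figure, so BMI data or a pilot control arm should not be presumed. Use the PASI scale that will be analysed, which first requires section 2.19.1 to settle between absolute and percentage change.
5. Quote joint power only if the protocol states that both endpoints must succeed.
6. Align the sentence in section 4 with the revised basis.

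The cost is a short recalculation and some rewording. Endpoints, analysis and recruitment are unchanged. The drawback is that the stated power for BMI may look less favourable than the present 80% suggests.

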### Intervention

2.12

All participants will receive standardized baseline care. For skin lesions and xerosis, urea vitamin E cream (Fuyuan Pharmaceutical Co., Ltd., National Medicine Permit No. H34022160) will be applied as a moisturizer. Additionally, all patients will undergo health education regarding lifestyle and dietary modifications, along with training in daily skin care. To enhance adherence and objectively monitor compliance, researchers will add all participants to a WeChat health management group.

Participants will be instructed to photograph their daily meals; the images will be analyzed via a dedicated mobile application to estimate caloric intake. Daily step counts will be automatically recorded and tracked through the WeChat sports mini-program.

Throughout the trial, participants may continue their usual medications for comorbidities (e.g., diabetes, hyperlipidemia). We will require them to maintain the same types and doses of their underlying disease medications during the trial, with any changes in medication recorded at each visit. However, the use of any treatments specifically targeting psoriasis is prohibited.

(1) Experimental group:

In addition to conventional care, patients in the verum group will receive true catgut embedding acupuncture (needle insertion followed by thread embedding), at the following points: CV12 (Zhongwan), CV4 (Guanyuan), SP15 (Daheng), ST25 (Tianshu), ST36 (Zusanli), BL20 (Pishu), BL18 (Ganshu), and SP10 (Xuehai). All points are needled bilaterally except for CV 12 and CV 4. These acupoints were selected based on a comprehensive review of prior literature and established clinical expertise. This combination is designed to simultaneously address psoriatic inflammation and underlying metabolic dysfunction. Previous studies suggest that points such as ST25 (Tianshu), SP15 (Daheng), CV12 (Zhongwan), ST36 (Zusanli), and BL20 (Pishu) can help improve central obesity and gastrointestinal function (41, 42), while SP10 (Xuehai) is traditionally used to activate blood circulation and resolve stasis, and BL18 (Ganshu) is employed to promote blood circulation and regulate qi.

The acupoints were localized according to the World Health Organization Standard Acupuncture Point Locations. All acupuncture point locations are shown in Figure 2.

*CV12*: On the anterior midline, 4 cun superior to the umbilicus.*CV4*: On the anterior midline, 3 cun inferior to the umbilicus.*SP15*: 4 cun lateral to the umbilicus, level with the umbilicus.*ST25*: 2 cun lateral to the umbilicus, level with the umbilicus.*ST36*: On the anterior aspect of the leg, 3 cun inferior to the lateral depression of the knee joint (Lateralmere, ST35) and one finger-breadth lateral from the anterior crest of the tibia.*BL20*: On the back, at the level of the lower border of the spinous process of the 11th thoracic vertebra (T11), 1.5 cun lateral to the posterior midline.*BL18*: On the back, at the level of the lower border of the spinous process of the 9th thoracic vertebra (T9), 1.5 cun lateral to the posterior midline.*SP10*: On the medial aspect of the thigh, with the knee flexed, 2 cun superior to the medial superior border of the patella, on the bulge of the medial portion of the quadriceps muscle.

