### Research objectives

2.4

*Primary objective*: to evaluate the efficacy of ACE therapy as an adjunctive treatment for improving the PASI score and reducing BMI after 8 weeks in patients with mild psoriasis and overweight.*Secondary objectives*: (1) to assess the changes in secondary efficacy indicators of psoriasis, BMI, waist circumference (WC), WHR and metabolic-related indicators, etc. measures from baseline to week 8. (2) to document the incidence of adverse events (AEs) throughout the study period. (3) to determine the psoriasis recurrence rate during the follow-up period.

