### Withdrawal criteria

2.8

Participation will be discontinued if any of the following criteria are met:

(1) Failure to attend scheduled outpatient follow-ups on time.(2) Occurrence of serious adverse reactions.(3) Changes in the participant’s medical condition that render continued participation inappropriate.(4) The participant or their legal guardian requests to stop.

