**Figure 3 fig3:**
[figure not shown]
ACE needle and absorbed sutures.

For the verum group, the needle will be inserted manually into the selected acupoints. The ST25, SP15, CV12 and ST36 will be punctured perpendicularly, with an insertion depth of approximately 25–35 mm. The BL18 and BL20 will be punctured at a 45°angle to the skin, with an insertion depth of about 15–20 mm. Once the acupoint sensation is achieved, the practitioner withdraws the needle while pushing the absorbable thread into the muscle layer using the needle core. Immediately following, needle withdrawal, the puncture sites will be promptly compressed with sterile dry cotton swabs to prevent bleeding. The placement of the thread depends on the depth of the needling, and the practitioner will not feel any resistance while inserting the absorbable thread. The treatment will be administered once every 2 weeks for a total of four sessions, lasting 8 weeks (24, 34).

For the sham group: using the same disposable needles (with the catgut suture pre-removed), the practitioner performed an identical procedure—insertion into the muscle layer followed by a simulated “pushing-withdrawing” action—ensuring the same tactile experience for participants as the verum group, with the sole difference being the absence of actual suture embedding.

A sham procedure was selected as the control for​ the following reasons: (1) to ensure rigorous trial design: as a double-blind, randomized controlled trial, a sham procedure is essential. It matches the verum ACE in every visible aspect, ensuring effective participant blinding and controlling for non-specific effects (e.g., placebo, natural disease variation). This allows for an objective evaluation of the specific therapeutic effect attributable to the catgut embedding itself. (2) to demonstrate specific efficacy beyond standard care limitations: Current standard treatments for mild psoriasis have limitations, including side effects and lack of efficacy for obesity. This trial aims to prove that ACE offers a specific therapeutic benefit, which necessitates comparison against a non-active intervention to establish its distinct clinical value.

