### Data collection procedures

2.15

The study comprises an 8 weeks intervention period followed by a 32-week follow-up phase. During the intervention, data collection and clinical assessments will occur biweekly. Post-intervention follow-up evaluations are scheduled every four weeks through week 24, with a final assessment at week 32.

To explore the biological underpinnings of the therapeutic response, peripheral venous blood samples will be collected at baseline (week 0), mid-intervention (week 4), end-of-treatment (week 8), and at the final follow-up (week 32). These supplementary samples will support exploratory multi-omics analyses, including single-cell sequencing, untargeted metabolomics, and proteomics (Figure 4). A comprehensive schedule of all assessment items is provided in Table 1.

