Our selection criteria were carefully dictated by both methodological rigor and ethical feasibility. We specifically enrolled patients with mild psoriasis (PASI < 3 or BSA < 3) because the trial design required a baseline topical treatment of only simple emollients (urea ointment). Excluding moderate-to-severe cases was an intentional ethical decision to avoid interfering with the intensive standard-of-care therapies those patients require, which would have confounded the specific therapeutic signal of ACE. Furthermore, the BMI inclusion threshold was set at ≥ 24 kg/m^2^ to ensure recruitment feasibility; a more restrictive cutoff (e.g., ≥ 30 kg/m^2^) would have unnecessarily limited the participant pool and underpowered the study without changing the underlying biological premise of metabolic-driven inflammation.

The methodological strengths of this trial are characterized by its multicenter framework and the implementation of specific protocols designed to mitigate performance bias—a persistent challenge in acupuncture-related blinding. By utilizing pre-loaded delivery devices and third-party randomization, we prioritized internal validity to ensure the reliability of the therapeutic signal. Beyond its rigorous design, this study addresses a significant gap in existing literature by incorporating an extended 32-week follow-up phase. This longitudinal perspective is essential for evaluating whether metabolic adjustments are sustained and how they influence long-term disease recurrence patterns. Furthermore, the integration of high-resolution molecular analyses—including single-cell sequencing and proteomics—allows for a granular investigation into the systemic crosstalk between metabolic health and cutaneous immune homeostasis. By moving beyond clinical observation, these exploratory findings may elucidate the biological pathways through which ACE modulates the psoriasis-obesity phenotype, offering a mechanistic foundation for integrative therapeutic strategies.

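### The ban on psoriasis treatment has no stated end and is not reconciled with the recurrence objective or with the exit rule for participants who worsen in follow-up

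*Protocol article*

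**What the plan says.** Section 2.12 (Intervention) opens the relevant paragraph with "Throughout the trial, participants may continue their usual medications for comorbidities (e.g., diabetes, hyperlipidemia" and similar examples, asks for stable doses of those drugs, and then adds: "However, the use of any treatments specifically targeting psoriasis is prohibited". The sentence has no end date.

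On timing, section 2.13 says "The treatment will be administered once every 2 weeks for a total of four sessions, lasting 8 weeks". Section 2.15 says "The study comprises an 8 weeks intervention period followed by a 32-week follow-up phase", and then "Post-intervention follow-up evaluations are scheduled every four weeks through week 24, with a final assessment at week 32". Tables 1 and 2 also stop at week 32.

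Section 2.4 makes it a secondary objective "to determine the psoriasis recurrence rate during the follow-up period", and the Discussion presents the long follow-up as the means of studying recurrence.

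The Discussion explains that mild patients were chosen because the design allowed only an emollient as background topical care. It continues: "Excluding moderate-to-severe cases was an intentional ethical decision to avoid interfering with the intensive standard-of-care therapies those patients require". It adds that such therapies would have confounded the effect of the embedding.

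The rule that could cover worsening is the third criterion of section 2.8, repeated at the end of 2.13: "Changes in the participant’s medical condition that render continued participation inappropriate". It names neither psoriasis nor a threshold. Section 2.8.1 then takes the withdrawn participant's last observation as the final outcome. Section 2.21 closes with a complete-case approach without imputation, although the same section earlier prefers multiple imputation or mixed models.

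**The concern.** The plan sets out to count an event, recurrence, in a period when its own text appears to forbid treating that event. The reason it gives for withholding treatment is tied to mild disease. For a participant who becomes worse than mild, that reason no longer applies, yet the ban has no stated limit and no section links the two. Sites would have to choose for themselves between leaving the participant untreated, recording a deviation, and discontinuing.

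The statistical stake is informative loss of data. If worsening leads to discontinuation, follow-up stops because of the outcome that the third secondary objective measures. The week 12 to 32 summaries then depend on which path each site took, and on which of several missing-data statements is applied.

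**Working it through.** **1. Unaffected figure.** The sample size reproduces from section 2.11: (1.96 + 0.84)² × [0.60 × 0.40 + 0.25 × 0.75] / (0.60 − 0.25)² = 7.84 × 0.4275 / 0.1225 = 27.36, rounded up to 28. Then 28 / 0.80 = 35 per group. Nothing in this point changes it.

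**2. How long the ban lasts.** The intervention ends at week 8 and the last scheduled assessment is at week 32. If the ban runs to that visit, 32 − 8 = 24 weeks fall after the intervention, and 24 / 32 = 75%. Read literally, section 2.15 gives 8 + 32 = 40 weeks, but no assessment is scheduled after week 32, so week 32 is used here.

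**3. The sections side by side.**

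| Situation in follow-up | Ban (2.12) | Ethical rationale (Discussion) | Exit and data rule |
|---|---|---|---|
| Relapse that stays within mild disease | Applies, if it covers follow-up | Still fits | None specific |
| Progression beyond mild disease | Applies, if it covers follow-up | Does not reach this participant | General criterion in 2.8; then last value (2.8.1) or complete case (2.21) |

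The gap is in the second row. Section 2.14 adds clinical observation after the intervention, and evaluation with follow-on care when discomfort or an adverse reaction is reported. It does not say whether the ban ends or whether assessments continue.

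**4. Direction of the distortion.** Let an arm have *n* participants, of whom *r* have a recurrence, and let *w* of those *r* be withdrawn without the recurrence being recorded.

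- True proportion: r/n.
- Last value carried forward, taken before the recurrence: (r − w)/n. Shortfall: w/n.
- Complete case: (r − w)/(n − w). Shortfall: w(n − r)/[n(n − w)], which is positive whenever w > 0 and r < n.
- Recurrence recorded at an exit visit and carried forward: the count r/n is kept, but the week 32 severity is frozen at the exit value.

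With n = 35, each participant carried forward without a recorded recurrence lowers the proportion by 1/35 = 2.9 percentage points. With the 28 left after the assumed 20% dropout, it is 1/28 = 3.6 points. The article gives neither r nor w, so no total can be computed.

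**5. Safety reporting.** Section 2.17 collects adverse events regardless of relationship, and Table 2 schedules them through week 32. The rate formula in 2.21 counts only reactions attributed to treatment. Worsening of psoriasis judged unrelated would be collected but would not enter that rate.

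**The case against.** The strongest reply is that the rules work in sequence. Treatment is barred; a participant for whom staying in is no longer appropriate is discontinued; section 2.14 provides care. No two rules demand opposite actions. This stands. A reader might infer that the article contradicts itself, but it shows an unreconciled path and not a contradiction.

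Four further points carry weight:

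- The extension to week 32 is an inference. The words about the whole trial belong to the sentence on comorbidity drugs. It is the natural reading, but it is not stated.
- A reader might take mild disease to be the only justification for emollient-only care. The Discussion runs the other way (the design needed emollients, so mild patients were chosen) and also cites confounding.
- Relapse is not the same as leaving the mild range, and no section says that relapse triggers withdrawal. One could assume that 20 to 40% relapse and all leave, giving 7 to 14 of 35 per arm, but that rests on a relapse rate and a rule that the article does not contain.
- Data on exit are not all lost. Section 2.8.1 retains what was collected, and 2.18 offers an early termination visit, with consent, covering efficacy, safety, reasons and medication. A relapse that prompts withdrawal can be captured there, though not its later course.

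It can also be said that the full protocol, a supplement not shown here, may hold the missing detail. That would excuse silence. It does not remove the problem that the ban, the recurrence objective, the rationale, the exit rule and the carry-forward rule are all printed here and do not fit together for a participant who worsens.

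**Conclusion.** The point holds in limited form. The ban is open-ended and most naturally covers follow-up, recurrence is an aim of that period, and the ethical rationale stops at mild disease. The only written exit ends participation and then freezes or drops the participant's later data. This can bias the recurrence rate and the week 12 to 32 descriptions.

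The size is bounded by context. Section 2.21 makes those later time points descriptive, without between-group tests. The week 8 comparison is affected only if worsening before week 8 leads to withdrawal or treatment. Power and sample size do not change. Each unrecorded recurrence costs about 3 percentage points per arm, and the number of such cases is unknown. The conclusion assumes that the ban extends past week 8; if the full protocol ends it there, what remains is how data after relapse or after treatment are handled. It is a cheap improvement worth making, not a threat to the primary result.

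**What to change.** 1. Reconcile sections 2.4, 2.8 (and its repeat in 2.13), 2.12, 2.14 and the Discussion on how long the prohibition applies and how it relates to worsening. Which treatment rule applies is for the investigators; none is proposed here.
2. Whatever the rule, separate the end of treatment compliance from the end of assessment. Participants who worsen or start psoriasis treatment should continue the scheduled visits to week 32, with consent, in place of stopping data collection and carrying the last value forward. This matches the intention-to-treat commitment in 2.21.
3. Record the date and type of the first psoriasis treatment. Section 2.12 already records medication changes at each visit, so this is a small addition.
4. Report worsening of psoriasis in the adverse event summary regardless of attribution.
5. Do not define recurrence as exceeding the mild limits. That would count participants who never improved and miss relapse within the mild range. The limits are also unsettled: the abstract lists the PASI and BSA thresholds together, while section 2.5 joins them with an or.

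The cost is protocol wording and one case report form field. The downside is that some week 12 to 32 values will come from treated participants; the recorded date identifies them.
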